### Statistical analysis

The Statistical Product and Service Solutions (SPSS) statistical package program (version 20.0, SPSS Inc., Chicago, Ill., USA) will be used to analyse data in the CTU of Children’s Hospital affiliated with Fudan University by statisticians. All analyses, including those from any participants who drop out during the trial, will be based on the intention-to-treat (ITT) principle using the last observation carried forward rule. Missing values will be handled by the mixed model for repeated measurements. Baseline information will be collected before randomization and includes the gender and age of patients, disease course, clinical type, GMFCS level, primary outcome (GMFM, FMFM) and secondary outcomes (PEDI, CP-QOL). Descriptive statistics will be used to detail baseline participant demographics and the general status of patients, such as gender, age, disease course, clinical type and GMFCS level. Variables will be checked for normal distribution and presented as mean +/− the standard deviation and compared by Student *t* test when normally distributed. For variables not normally distributed, the data will be expressed as median +/− the interquartile range, and non-parametric tests will be used. Categorical variables will be expressed as number (%) and analysed by *χ*^2^ tests or Fisher’s exact tests, when appropriate. The mixed effect model will be used to analyse the between-group difference in repeated measures for the two primary outcomes and other outcomes (GMFM, FMFM, PEDI and CP-QOL scores) across five testing time points (weeks 0, 4, 8, 12 and 24). Mean group difference and 95% confidence intervals will be reported. Safety analyses will be compared with the incidence of AEs in the two groups using the *χ*^2^ test. A *p* value of < 0.025 will be considered as statistically significant for the two primary outcomes.

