### Sample size calculation

Sample size calculations were performed based on the two primary outcomes. According to our pilot trial, we assume that, after 12 weeks of treatment, the mean change in the GMFM scores in the experimental group will be greater than the control group with a mean difference of 2.4 and a standard deviation of 3.0. At an alpha level of 0.025, 40 subjects will be required for each group to ensure a statistical power of 0.9. Assuming 20% drop out, a total of 100 participants will be needed to achieve statistical significance, so each group is required to have 50 initial participants.

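### Last observation carried forward and a mixed model are both ordered for the same missing data; carrying scores forward leaves the model nothing to handle and biases the 12-week effect

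*Protocol article*

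**What the plan says.** Three statements in the Statistical analysis section of the protocol article bear on missing data:

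- The scope of the first rule is "All analyses, including those from any participants who drop out during the trial", and the rule itself is that these "will be based on the intention-to-treat (ITT) principle using the last observation carried forward rule".
- The next sentence gives a second rule: "Missing values will be handled by the mixed model for repeated measurements".
- Later in the same section: "The mixed effect model will be used to analyse the between-group difference in repeated measures for the two primary outcomes and other outcomes", fitted "across five testing time points (weeks 0, 4, 8, 12 and 24").

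Neither rule is called primary or sensitivity, and neither is tied to an outcome or to a type of missingness. The Sample size calculation section expects a larger 12-week gain in GMFM on acupuncture, "with a mean difference of 2.4 and a standard deviation of 3.0". It also plans for losses: "Assuming 20% drop out, a total of 100 participants will be needed".

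**The concern.** As written, the rules collide. LOCF applied to all analyses fills every missing visit after the first, so the mixed model receives a complete data set in which carried scores count as measurements. ITT does not require this. It fixes which children are analysed and in which arm, not how a missing score is filled.

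LOCF also suits this trial badly. It assumes that a motor score stops moving at the last visit. Under the Inclusion criteria and Interventions sections the children are 12 to 72 months old and both arms have rehabilitation three times a week, so some gain is expected in both arms. Dropouts are then credited with too little change.

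- With equal dropout, the between-arm difference shrinks and power is lost.
- With unequal dropout, the arm that loses more children is penalised more, so the bias can favour either arm and type I error can rise. Unequal dropout is plausible here because only the outcome assessor and data analyst are described as blinded and the allocated control treatment contains no acupuncture.

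The conflict reaches both primary outcomes and both secondary outcomes. Two statisticians could each follow the section and report different estimates.

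**Working it through.** **1. The plan's own figure.** Inputs from the Sample size calculation section: difference 2.4, SD 3.0, alpha 0.025, power 0.90, dropout 20%. The normal formula, two-sided, is

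n = 2(z₀.₉₈₇₅ + z₀.₉₀)² × 3.0² / 2.4² = 2(2.241 + 1.282)² × 1.5625 ≈ 38.8, so 39 per arm.

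The t-test version gives 40.07, in line with the stated 40. Then 40 / (1 − 0.20) = 50 per arm. The sample size reproduces with alpha two-sided.

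**2. Expected difference under LOCF.** Let C be the control gain over 12 weeks (not given in the article), Δ the true difference, dT and dC the dropout on acupuncture and control, and f the share of the gain already reached at the last visit. With linear gain, an arm with dropout d keeps the share g(d) = 1 − d + d·f of its gain, so

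estimate = (C + Δ)·g(dT) − C·g(dC).

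If dropouts are last seen at baseline, week 4 or week 8 with equal chance, f averages (0 + 1/3 + 2/3)/3 = 1/3. The table assumes C = 3. The last column comes from simulated trials: 50 per arm, residual variance 4.5 so that the change SD is √(2 × 4.5) = 3.0, and a t test on the LOCF change at week 12 at two-sided 0.025.

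| Dropout, acupuncture / control | True Δ | Expected estimate | Simulated rejection rate |
|---|---|---|---|
| 20% / 20% | 2.4 | 2.4 × 0.867 = 2.08 | 84% (completers only: 90%) |
| 20% / 20% | 0 | 0 | 2.6% |
| 15% / 25% | 0 | 3 × 0.900 − 3 × 0.833 = +0.20 | 3.5% |
| 10% / 30% | 0 | 3 × 0.933 − 3 × 0.800 = +0.40 | 6.0% |
| 15% / 25% | 2.4 | 5.4 × 0.900 − 3 × 0.833 = 2.36 | 93% |
| 25% / 15% | 2.4 | 5.4 × 0.833 − 3 × 0.900 = 1.80 | 70% |
| 30% / 10% | 2.4 | 5.4 × 0.800 − 3 × 0.933 = 1.52 | 54% |

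**3. Dependence on the assumptions.**

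- *Timing.* With 20% dropout in both arms, the estimate is 1.92, 2.08 or 2.24 if all dropouts were last seen at week 0, 4 or 8. C cancels here.
- *Control gain under the null.* With dropout 10% / 30%, type I error is 2.4% at C = 0, 3.1% at C = 1, 4.1% at C = 2, 6.0% at C = 3 and 8.4% at C = 4.
- *Control gain with a true 2.4.* For C from 0 to 6 and the same three last visits, 30% / 10% gives 0.48 to 2.16, and 10% / 30% gives 2.16 to 3.36. In the second case the effect is overstated when 0.3·C > 0.1·(C + 2.4), that is, when C > 1.2.

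**4. The mixed model without LOCF.** A separate simulation used 3,000 trials per scenario, random slopes, C = 4 and dropout completely at random. A likelihood-equivalent analysis of the observed data gave 2.40 to 2.41 for a true 2.4, and 0.00 to −0.01 for no effect. On the same data LOCF gave 2.09 (20% / 20%), 1.38 (30% / 10%) and 2.78 (10% / 30%).

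**The case against.** The strongest reply is that the sentences can be reconciled: LOCF for children who drop out, the mixed model for other missed visits. The article does not say so, and the first rule covers all analyses. Even on that reading LOCF still governs the dropouts, where the bias arises.

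Other points narrow the concern without removing it:

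- The model itself is fixed. What remains open is whether it is fed filled or observed data, and the data analyst is blinded.
- The article gives 20% dropout without a split, so a threefold imbalance is illustrative. Some features may limit imbalance: the same rehabilitation schedule in both arms, free choice of acupuncture in weeks 12 to 24, and an adherence programme not restricted to one arm.
- Type I error is inflated only if dropout is unequal and controls would have gained after their last visit. With no control gain it is nominal.
- The simulations test week-12 change, not the planned model. But once LOCF has made the data complete, a model with separate arm-by-visit means returns the same difference in mean change, so the bias in the estimate carries over.
- Children who leave rehabilitation may gain less than those who stay, and the mixed model relies on data missing at random. That is a reason for a sensitivity analysis, not for LOCF.

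**Conclusion.** The concern holds. The section orders two missing-data rules without scope or priority, and nothing elsewhere in the article resolves them. On the article's own 20% dropout, taken as equal in both arms with linear gain and last visits spread evenly, LOCF turns a true 2.4 into 2.08. It lowers power to 84%, when simply analysing completers would give the planned 90%; type I error stays near 2.5%. Unequal dropout is the more serious risk, but its size rests on assumptions about control gain and dropout split. Under the null at 10% / 30%, type I error runs from nominal with no control gain to 8.4% with a gain of 4 points. With a true 2.4 at 30% / 10% and a gain of 3 points, the estimate is 1.52 with 54% power. The sample size is not affected.

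**What to change.** Delete the LOCF clause and separate the analysis population from the handling of missing data, for example: *All randomised children are analysed in the arm to which they were allocated. The primary analysis is the likelihood-based mixed model for repeated measures fitted to the observed data, assuming data missing at random, with no single imputation.* If LOCF is kept at all, label it a sensitivity analysis. A better one would allow for data missing not at random, such as delta-adjusted or reference-based multiple imputation; this is advisable but not needed to resolve the contradiction, and its details can sit in the SAP. Make the change before outcome data by arm are seen. The cost is protocol and SAP wording only: the mixed model is already planned, and neither the sample size nor the data collection changes.

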### Study design

This is an outcome assessor and data analyst-blinded, randomized, controlled superiority trial. The study is planned to be conducted from 1 January 2019 to 31 December 2021 in the Children’s Hospital of Fudan University. CP patients with motor dysfunction meeting the inclusion criteria will be allocated in a 1:1 ratio into either an acupuncture treatment group or a control group. CP patients in the control group will receive routine rehabilitation treatment, while the acupuncture group will receive a combination of routine rehabilitation treatment and scalp acupuncture. The Gross Motor Function Measure (GMFM) and the Fine Motor Function Measure (FMFM) will be assessed as primary outcome measures. The Paediatric Evaluation of Disability Inventory (PEDI) and the CP-Specific Quality of Life Scale (CP-QOL) will be selected as secondary outcome measurements. All assessments will be conducted at baseline, week 4 (treatment 12), week 8 (treatment 24), week 12 (treatment 36) and week 24 (follow-up). Figure 1 summarizes the flow of the entire trial. Figure 2 shows the study timeline, according to the Standard Protocol Items: Recommendations for Interventional Trials (SPIRIT) diagram. Additional file 1 presents the SPIRIT checklist.

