### Interventions

The study is a randomized clinical trial carried out in outpatient rehabilitation departments of four hospitals. A total of 100 children with CP will be recruited. The patients will be randomly assigned to two different groups: 1) the treatment group and 2) the control group. The treatment group (*n* = 50) will receive routine rehabilitation treatment combined with scalp acupuncture three times per week for 12 weeks, while the control group (n = 50) will receive routine rehabilitation treatment three times per week for 12 weeks. Both groups will be evaluated at baseline, week 4 (treatment 12), week 8 (treatment 24), week 12 (treatment 36) and week 24 (follow-up). Both groups will receive routine CP rehabilitation treatment over the course of the 12-week study period. The routine rehabilitation program was designed according to the Chinese CP rehabilitation treatment guidelines, which include physical therapy (PT) and occupational therapy (OT) for 3 days a week [21]. Chinese herbal medicine and Chinese patent drugs will be prohibited during the trial.

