### Participant recruitment

Participants will be recruited in four hospitals (Children’s Hospital of Fudan University, The 445th Hospital of Chinese People’s Liberation Army, Huajing Community Health Service Centre of Xuhui District and Jiangchuan Community Health Service Centre of Minhang District) in Shanghai, China. Prospective participants will be asked to meet with the study coordinator to discuss the study and provide information about the eligibility criteria. If children with CP are eligible and their parents/guardians are interested in participating, they will be invited for a series of rehabilitation assessments after being diagnosed by neurologists. One hundred children with CP will be included in the study. When their informed consent has been obtained, children with CP will be randomized into two groups with different treatments [10].

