### Randomization and allocation concealment

The recruited patients will be randomly assigned to either the experimental group or the control group according to a randomization and allocation plan. This allocation will be done using a computer-generated, block randomization (block size of 4 and 1:1 allocation) prepared by an independent epidemiologist not otherwise involved in the trial. A computer-generated block randomization process designed by the CTU is used to allocate participants to the treatment group or the control group in a 1:1 ratio (block size = 4). The randomization list is kept strictly confidential. Allocation concealment is ensured with the use of sequentially numbered (block number and sequence number), identical, opaque, sealed envelopes. Computerized randomization preserves allocation concealment and reduces the possibility of selection bias since the research assistant is kept unaware of the group assignments until after the participants are allocated to groups.

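### Four sites recruit and treat, but neither the described randomisation nor the described mixed model mentions centre; adding centre to the model costs little and is correct whichever way the lists were built

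*Protocol article*

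**What the plan says.** - **Setting.** Under Participant recruitment: "Participants will be recruited in four hospitals". The list that follows names the university children's hospital, a military hospital and two community health service centres. Under Interventions, the trial is "carried out in outpatient rehabilitation departments of four hospitals", and the abstract also gives four centres. Under Study design, however, the trial is to run until "31 December 2021 in the Children’s Hospital of Fudan University", which names one site only.
- **Randomisation.** Under Randomization and allocation concealment: "This allocation will be done using a computer-generated, block randomization (block size of 4 and 1:1 allocation". Envelopes are numbered by block and sequence. No stratification factor or site code is given, and nothing says whether there is one list or one per site.
- **Analysis.** Under Statistical analysis: "The mixed effect model will be used to analyse the between-group difference in repeated measures for the two primary outcomes and other outcomes", over weeks 0, 4, 8, 12 and 24. Group and time are the only elements described. Centre is also absent from the listed baseline variables. The threshold is a p "value of < 0.025 will be considered as statistically significant for the two primary outcomes".
- **Sample size.** "At an alpha level of 0.025, 40 subjects will be required for each group to ensure a statistical power of 0.9", from a GMFM difference of 2.4 and an SD of 3.0. The article does not say whether that SD includes variation between centres.

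**The concern.** Both arms receive rehabilitation as background treatment, delivered in the outpatient department of each site. Centre is therefore a plausible prognostic factor, although the article offers no data on this.

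The two possible list structures have different consequences. A single list across four sites balances the arms overall but not within a site, so differences between hospitals add noise to the treatment comparison. Per-site lists balance the arms within each site, but an analysis that then ignores centre uses a standard error that is too large. The article does not let a reader tell which design was run, so the reader cannot tell which consequence applies. At stake is the precision and calibration of the two primary tests, not their protection against false positives.

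**Working it through.** **Inputs from the article:** difference 2.4, SD 3.0, alpha 0.025, power 0.9, 40 evaluable per arm, 20% dropout, 1:1 in blocks of 4, four sites.

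**Assumptions, because the article gives no figure:** centre explains 0, 10 or 20% of the variance in change; centres are of equal size unless stated. The check uses a single week-12 change score, not the full repeated-measures model.

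**1. The plan's own figure.** n per arm = 2(z₀.₉₈₇₅ + z₀.₉₀)²(3.0/2.4)² = 2 × (2.241 + 1.282)² × 1.5625 = 38.8, so 39. The exact two-sided t-test at 40 per arm has power 0.899. With dropout, 40/0.8 = 50 per arm and 100 in total. The stated sample size reproduces on a two-sided 0.025 test.

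**2. Chance imbalance with a single list.** Take 25 children per centre, 50 of 100 allocated to acupuncture, and centres arriving in random order. The SD of the number on acupuncture in a centre is √(25 × 0.5 × 0.5 × 75/99) = 2.18. By simulation, the chance that at least one centre splits 16:9 or worse is about 0.45, and 17:8 or worse about 0.20.

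**3. How far such a split can move the estimate.** A 16:9 split puts 16/50 − 9/50 = 0.14 more of one arm in that hospital. At 10% centre variance the centre SD is 3.0 × √0.10 = 0.95. A hospital one SD from the rest then shifts the treatment difference by 0.14 × 0.95 = 0.13 points. At 20% the shift is 0.14 × 1.34 = 0.19. The planned effect is 2.4.

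**4. Type I error, single list, centre ignored.** Simulated values were 0.023 to 0.026 for centre variance from 0 to 20%, with equal centres (20 each) and unequal centres (44/20/8/8). This is nominal.

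**5. Power, single list (total SD 3.0, 80 evaluable).** If adjustment removes the centre share, the SD becomes 3.0√(1 − share). The normal approximation then rises from 0.909 to 0.937 (10%) or 0.961 (20%), a gain of 2.8 or 5.2 points before the cost of imbalance and lost degrees of freedom. Simulation includes those costs:

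| Centre share | Without centre | With centre |
|---|---|---|
| 0% | 0.899 | 0.888 |
| 10% | 0.894 to 0.906 | 0.916 |
| 20% | 0.892 to 0.909 | 0.946 |

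Ranges are over two simulations of equal centres (the 0% row comes from one of them). The gain is about 1 to 2 points at 10% and 4 to 5 at 20%. At 0% there is a cost of about 1 point.

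**6. Per-site lists, centre ignored.** The arms are balanced within centres, so the true standard error is smaller than the one used by the factor √(1 − share). The true error is approximately P(|Z| > 2.241/√(1 − share)): 0.018 at 10% and 0.012 at 20%. Simulations with equal centres gave 0.017 to 0.019 at 10% and 0.012 to 0.016 at 20%. With 44/20/8/8 the values were 0.022 and 0.019. All lie below 0.025. Power with equal centres was 0.904 to 0.912 without centre against 0.923 to 0.927 with it at 10%, and 0.916 to 0.924 against 0.950 to 0.956 at 20%.

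**The case against.** The strongest reply is that the model half argues from silence. The article lists no model terms at all, covariates are commonly left to a full protocol or SAP, and nothing says that centre is excluded. That stands: silence about centre in the model would not be a finding by itself. The randomisation, however, is described in detail without a centre factor, and the mismatch between one hospital and four is in the article itself.

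A second reply is that power without centre stays at or near the planned 0.90. This is right if 3.0 is the total SD, so the loss is then a gain forgone and not a shortfall. If 3.0 is a within-centre SD, leaving centre out gives about 0.876 at 10% and 0.831 at 20% (normal approximation, against 0.909). The article does not say which applies.

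A reader might also infer more than the documents support:

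- **An inflated or generally mis-stated error rate.** With a single list the error is nominal; with per-site lists it is conservative.
- **One shared envelope series.** The article does not say so, nor where the envelopes are held or opened.
- **Very different hospitals, each with its own rehabilitation and case-mix.** This is inferred from the types of site. The article sets one guideline-based programme with a common frequency and session length, and common staff training.
- **A hospital effect passing for an acupuncture effect.** Step 3 shows shifts of 0.13 to 0.19 points for a 16:9 split under the stated assumptions, small beside 2.4.

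**Conclusion.** The point holds at minor to moderate severity. Four sites recruit and treat, the described randomisation has no centre stratum and leaves the list structure open, and the described analysis does not mention centre.

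If there is one list, the consequence is lost precision: about 2 to 5 power points at an assumed 10 to 20% centre variance (nearer 1 to 4 in the simulation with lower gains), and none if centre is not prognostic. If lists are per site and centre is ignored, the consequence is a conservative test. No false-positive risk is shown in either case, and the sample size itself reproduces. The sizes depend on assumed centre variance and centre sizes. The direction does not, and including centre is appropriate under both list structures.

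**What to change.** 1. In Statistical analysis, include centre (four levels, small sites pooled if needed) as a fixed effect in the mixed models for GMFM, FMFM, PEDI and CP-QOL, fixed before unblinding. If an SAP already does this, a cross-reference is enough. Cost: three degrees of freedom, no extra patients or data, and about 1 power point if centre proves unrelated to outcome under a single list.
2. In Randomization and allocation concealment, state whether the block-of-4 list is single or per site. Cost: one sentence.
3. Reconcile Study design, which names one hospital, with the abstract, Interventions and Participant recruitment, which give four. Cost: one sentence.

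A mid-trial switch to per-site lists should not be required. Recruitment began on 1 March 2019, so a switch would change the randomisation part-way through. Fixed blocks of 4 within a site are also easier to predict where only assessors and analysts are blinded.

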### Primary outcome measurement

The two primary outcomes of the study—Gross Motor Function Measure (GMFM) and Fine Motor Function Measure Scale (FMFM)—will be assessed at baseline, during the intervention period (at 4 weeks, 8 weeks and 12 weeks) and in the follow-up period (at 24 weeks).

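### GMFM and FMFM are tested at p < 0.025 but reported with 95% confidence intervals, so a primary interval can exclude zero for a result that the plan calls non-significant

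*Protocol article*

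**What the plan says.** Three statements in the protocol article bear on this.

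- **Decision rule (Statistical analysis).** For GMFM and FMFM, a *p* "value of < 0.025 will be considered as statistically significant for the two primary outcomes".
- **Interval (same section).** The mixed model is to estimate the "between-group difference in repeated measures for the two primary outcomes and other outcomes (GMFM, FMFM, PEDI and CP-QOL scores") over the five assessments. The next sentence reads "Mean group difference and 95% confidence intervals will be reported". No other level is named for the primary outcomes.
- **Sample size calculation.** The calculation is said to rest on both primary outcomes. It takes a GMFM change "with a mean difference of 2.4 and a standard deviation of 3.0", and continues: "At an alpha level of 0.025, 40 subjects will be required for each group" "to ensure a statistical power of 0.9". Whether 0.025 is one-sided or two-sided is not stated.

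**The concern.** A two-sided 95% interval excludes zero exactly when the two-sided p value is below 0.05. The primary outcomes are judged at 0.025. If that 0.025 is two-sided, test and interval disagree for every p value from 0.025 up to 0.05: the interval excludes zero and the plan's rule says not significant.

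The plan chose to control the error rate over two primary outcomes and sized the trial for the stricter level. The intervals, which many readers and later meta-analysts look at first, would not carry that control. A borderline result on one of the two scales could then be presented in two conflicting ways from the same analysis.

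**Working it through.** **Inputs.** From Sample size calculation: difference 2.4, SD 3.0, alpha 0.025, power 0.9, 40 per group, 20% dropout. From Statistical analysis: threshold 0.025 and interval level 95%. The documents give no correlation between GMFM and FMFM and no SD for FMFM, so the figures in points below are for GMFM only.

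**Step 1. Is 0.025 one-sided or two-sided?** This decides the matter, because a one-sided 0.025 would agree with a two-sided 95% interval. Normal approximation: n per group = 2 × SD² × (z_alpha + z_power)² / difference².

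- Two-sided 0.025: 2 × 9 × (2.241 + 1.282)² / 5.76 = 38.8, so 39. The two-sample t test needs 41.
- One-sided 0.025: 2 × 9 × (1.960 + 1.282)² / 5.76 = 32.8, so 33. The t test needs 34.

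The stated 40 lies between the two-sided results and six or more above the one-sided ones. At 40 per group and two-sided 0.025 the power is 0.909 (normal) or 0.899 (t), in line with the stated 0.9. Dropout: 40 / 0.8 = 50 per group, 100 in total, as stated. So 0.025 is two-sided, 0.05 / 2, and the matching interval level is 1 − 0.025 = 97.5%.

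**Step 2. Where test and interval disagree.** Standard error of the difference = 3.0 × √(2/40) = 0.671. With 78 degrees of freedom:

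| Interval | Critical t | Half-width (GMFM points) |
|---|---|---|
| 95% | 1.991 | 1.34 |
| 97.5% | 2.285 | 1.53 |

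An observed difference between about 1.34 and 1.53 points has a 95% interval that excludes zero and a p value above 0.025. The ratio of widths is 2.285 / 1.991 = 1.148. With normal critical values (1.960 and 2.241) the band is 1.31 to 1.50 and the ratio 1.144.

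**Step 3. How often this would happen, per outcome.**

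- No true effect: 0.05 − 0.025 = 2.5%.
- Planned effect of 2.4 points: 3.8% (normal) or 4.3% (t).
- Worst case: the band is 2.241 − 1.960 = 0.281 standard errors wide. The probability is largest when the true effect lies at its centre: 2 × Φ(0.281/2) − 1 = 11.2% (normal), or 11.5% by the t test. This is at a true effect of about 1.4 points, a little under 0.5 SD.

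**Step 4. What happens to the multiplicity control.** If neither outcome has an effect and the two estimates are independent:

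- Planned rule, p < 0.025 each: chance of at least one false positive 1 − 0.975² = 4.94%.
- Significance read from the 95% intervals: 1 − 0.95² = 9.75%. At an assumed correlation of 0.5 it is 9.1%.

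The second figure is not the error rate of the plan. It is the rate that would follow if the intervals were used in place of the stated rule.

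**The case against.** The case for leaving the text alone is a fair one. The decision rule is explicit, and the interval is given only as a reporting format. Nothing in the article makes exclusion of zero a criterion of success. Unadjusted 95% intervals beside an adjusted threshold are common, and they suit PEDI and CP-QOL. All of this stands, and it limits the point to one of reporting.

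Some stronger readings are tempting, and the document does not support them.

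- *A reader might infer that the false-positive rate of the trial is inflated to nearly 10%.* It is not. The tests keep 4.94% under independence, and 9.75% applies only to a rule that the plan does not contain.
- *A reader might infer that the intervals are too narrow.* A 95% interval labelled 95% has the right width for its label. It is narrower than the interval that matches the test.
- *A reader might fault the joint coverage of the two intervals as only about 90%.* The plan promises no joint coverage. The 90.25% is the figure under independence. Assumed correlations of 0.5 and 0.9 give 90.9% and 93.0%, and positive correlation is plausible because both scales are measured in the same children.

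One could also say that a separate interval level is a detail for the analysis plan. That does not remove the point: the article states both levels, and it is the two stated levels that do not match.

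**Conclusion.** The point holds as a minor one. For the same two primary contrasts, the plan fixes a decision rule at two-sided 0.025 and an interval at 95%, and the two conflict for 0.025 ≤ p < 0.05. Tests, estimates and sample size are not affected.

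The conflict itself rests only on reading 0.025 as two-sided, which the stated 40 per group supports. Its size rests on more: the figures in points and the chances away from no effect assume a two-sample t comparison at 40 per arm with SD 3.0. The planned analysis is a mixed model on all randomized children, whose standard error will differ, so these figures are illustrative. On that basis the conflict is uncommon for either outcome: 2.5% under no effect, about 4% at the planned effect, and not above about 11% whatever the true effect.

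**What to change.** Amend the interval sentence in Statistical analysis to give 97.5% confidence intervals for the confirmatory GMFM and FMFM contrasts and 95% intervals for PEDI and CP-QOL. If 95% intervals are also wanted for the primaries, for example for comparison with other trials, label them as unadjusted for multiplicity and not used to decide significance. State in the same place that 0.025 is two-sided.

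The cost is a sentence or two, settled before the data are unblinded. The primary intervals become about 15% wider. No patients, data or analyses are added.

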**Discussion:**

This is the first trial evaluating the efficacy and safety of scalp acupuncture as a treatment for motor dysfunction in children with cerebral palsy. The results of this trial are expected to provide relevant evidence demonstrating that scalp acupuncture can be used as an effective rehabilitation treatment method for improving motor dysfunction in children with cerebral palsy.

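### The only stated between-arm safety analysis is a χ² test of adverse-event incidence, with no interval or bound on risk; adding these would be a cheap improvement

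*Protocol article*

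**What the plan says.** The Discussion paragraph of the abstract states: "This is the first trial evaluating the efficacy and safety of scalp acupuncture as a treatment for motor dysfunction in children with cerebral palsy". The Objectives section speaks only of motor function, and no safety measure is listed among the primary or secondary outcomes.

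The Statistical analysis section deals with safety in one sentence: "Safety analyses will be compared with the incidence of AEs in the two groups using the" χ² test. The same section has a general rule for categorical variables, which are to be given as number (%) and analysed by χ² "tests or Fisher’s exact tests, when appropriate". It also promises "Mean group difference and 95% confidence intervals will be reported". That sentence directly follows the mixed-model analysis of the four scale scores, and a mean difference does not describe AE incidence.

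The Sample size calculation section fixes the trial's size on change in GMFM: "At an alpha level of 0.025, 40 subjects will be required for each group to ensure a statistical power of 0.9". After the dropout allowance it concludes "so each group is required to have 50 initial participants". No AE rate, safety margin or significance level for the AE test appears anywhere.

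The Safety section has every AE recorded with its degree and its causal relationship to acupuncture, and serious AEs reported at once. The Data collection, management and monitoring section provides monthly review by an independent DSMB with unblinded data.

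**The concern.** A test of difference can flag harm, but it cannot show how much harm remains compatible with the data. If it is the only between-arm safety result, the only reassuring output it can give is non-significance. In a trial of this size that output is likely for uncommon events even when the true risk has doubled.

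The intervention is an invasive add-on given over 36 sessions to children aged 12 to 72 months. The final report would be more useful if it said how large an AE risk the data can exclude. The data needed for that are already being collected.

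**Working it through.** **1. The plan's own figure.** Inputs from the Sample size calculation section: difference 2.4, SD 3.0, alpha 0.025, power 0.90, dropout 20%.

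n per arm = 2 × SD² × (z for 1 − α/2 + z for power)² / difference² = 2 × 9 × (2.2414 + 1.2816)² / 5.76 = 38.8, so 39. The plan states 40, and the t-based power at 40 is 0.899. Then 40 / 0.8 = 50 per arm and 100 in total. The figure reproduces with a two-sided alpha. No AE quantity enters it.

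**2. Miss rates of the AE test.** Inputs: 50 per arm (Sample size calculation) and 1:1 allocation (Study design). Assumptions, because the protocol gives no values: a two-sided 5% level and the pairs of risks below.

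For a events in one arm and b in the other, X² = ((a − b)/n)² / [p(1 − p) × 2/n], with p = (a + b)/(2n). The miss rate is the sum, over all (a, b) with X² below 3.841, of the two binomial probabilities multiplied together. The Fisher column uses p > 0.05 in place of the X² rule.

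| Control vs acupuncture risk (assumed) | Pearson, 50 per arm | Fisher, 50 per arm | Pearson, 40 per arm |
|---|---|---|---|
| 5% vs 10% | 85.5% | 93.7% | 85.4% |
| 10% vs 20% | 69.7% | 80.5% | 75.3% |
| 20% vs 40% | 40.5% | 48.5% | 50.3% |
| 30% vs 60% | 12.4% | 17.1% | 20.4% |
| 0% vs 5% | 76.0% | 96.2% | 86.2% |
| 0% vs 10% | 25.0% | 61.6% | 42.3% |
| 0% vs 15% | 4.6% | 21.9% | 13.0% |

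The first four rows are all doublings, and the miss rate runs from 86% down to 12% as the control risk rises. The 40-per-arm column shows the effect of the planned 20% dropout if only completers are counted.

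**3. Needling-specific events.** The Safety section lists retained needle and severe local pain after acupuncture, among others. Under the Interventions section, controls receive no acupuncture during the 12 treatment weeks, so their risk of such events is essentially zero. With 0/50 against x/50 the statistic reduces to X² = x / (1 − x/100). For x = 3 this is 3.09 (p = 0.079), and for x = 4 it is 4.17 (p = 0.041). Pearson therefore needs four events. Fisher needs six, because 5/50 vs 0/50 gives p = 0.056. Whichever way the test falls, it compares a real risk with one that is zero by design. The informative quantity is the acupuncture-arm risk itself.

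**4. What an interval adds.** Take 10/50 against 5/50.
- X² = 0.10² / (0.15 × 0.85 × 0.04) = 1.96, p = 0.16.
- The Wilson limits are 0.112 to 0.330 and 0.043 to 0.214.
- Newcombe lower limit = 0.10 − √[(0.20 − 0.112)² + (0.214 − 0.10)²] = −0.043.
- Newcombe upper limit = 0.10 + √[(0.330 − 0.20)² + (0.10 − 0.043)²] = 0.242.

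The test says only that the difference is not significant. The interval says that an excess of up to 24 percentage points is not excluded.

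With no events in 50 treated children, the exact upper limit is 1 − 0.025^(1/50) = 7.1% (two-sided 95%) or 1 − 0.05^(1/50) = 5.8% (one-sided 95%).

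**The case against.** The strongest reply has four parts.

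- **No safety rule is stated.** The protocol sets no safety hypothesis and does not say that a non-significant test will be taken as showing safety. A reader might infer that it plans to do so, but the text says only that incidences will be compared. This stands: the misreading is a risk, not a stated plan.
- **Low power is not general.** A reader might take 70% as the rate at which this design misses a doubling. That figure needs a control risk near 10%, which the protocol does not give. At 30% vs 60%, or at 0% vs 15% by Pearson, the test is quite sensitive. So one cannot say that the trial would most likely report no difference. This also stands.
- **Other safety provisions exist.** Causality recording, prompt reporting of serious AEs, monthly DSMB review, number (%) reporting and Fisher's test are all in the document, and they deserve credit. The monitoring provisions are data capture and oversight, and counts with a p value are still not an interval, so none of them supplies a bound on risk for the final report.
- **This is detail for the analysis plan, and trials are rarely powered for AEs.** The second half is right: sizing the trial on GMFM is no fault. On the first half, the exact interval method could well sit in an analysis plan that is not shown. But the article does state the safety method, and the method stated gives no estimate of harm, so it can be commented on here.

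**Conclusion.** The point holds as a cheap improvement, not as an error that undermines the trial. Safety is a named purpose in the abstract, and the only stated between-arm safety analysis is a significance test without an interval or bound. For uncommon events that test is weak at 50 per arm: it misses 86% at 5% vs 10%, 70% at 10% vs 20% and 76% at 0% vs 5%. For common events it is not weak: the miss rate is 12% at 30% vs 60%. All these figures rest on assumed risks and an assumed two-sided 5% level. A non-significant result could not by itself support a safety statement, and for needling-specific events the between-arm test is largely beside the point. The documents do not support a single miss rate for the design, nor the claim that the investigators intend to read non-significance as safety.

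**What to change.** In the Statistical analysis section, extend the safety sentence as follows.

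- Keep the χ² or Fisher p value as a descriptive figure.
- For any AE and for serious AEs, add to the number (%) of children per arm the risk difference with a Newcombe 95% confidence interval.
- For acupuncture-related and serious acupuncture-related AEs, report the acupuncture-arm risk with an exact (Clopper-Pearson) 95% upper bound, including when no events occur. State whether the bound is one- or two-sided.
- Say that the safety statement will rest on these intervals, and that a non-significant difference will not be read as evidence of safety.

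This needs no new patients and no new data, since causality and degree are already recorded. It costs a few table columns and a less favourable closing sentence: after no serious related events in 50 children, the report would state a risk below about 7% (two-sided bound) in place of no significant difference.
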